#### Secondary Outcome: The SWEMWBS

SWEMWBS, similar to WHO-5, is used to assess mental health and well-being by focusing on positive mental health aspects. It is a 7-item questionnaire, focusing on the past 2 weeks, covering aspects of both feeling good and functioning well, including optimism, relaxation, problem-solving, and interpersonal closeness. Each item is rated on a 5-point Likert scale from 1 (“none of the time”) to 5 (“all of the time”), with total scores indicating overall well-being; higher scores reflect greater well-being. Where the WHO-5 is an affective measure focusing on emotions and energy, the SWEMWBS is a hybrid measure that, in addition to measuring positive emotions, also includes aspects of functioning [38].

SWEMWBS is derived from the original 14-item version and is validated for screening mental well-being in both general and clinical populations, including young people, and has proven sensitive to changes [39].

#### Explorative Outcome: Intentions of Help Seeking

There is no standard approach for measuring intentions and barriers to help seeking, and existing studies have used a wide range of measures and definitions [5]. To retrieve a comprehensive measure of young people’s intentions of help seeking, we developed our own questions:

Imagine that you have been feeling very down over the past couple of months. Everything feels overwhelming, and you have started to feel that life is meaningless. How likely is it that you would seek help or support from the following if you found yourself in this situation? (1) Family, (2) Friends, (3) Partner, (4) A healthcare provider (e.g., doctor or psychologist), (5) Teacher, study counselor, manager, or HR., (6) Internet search (e.g. Google search or ChatGPT), (7) Social media (e.g., Instagram, TikTok and Reddit), (8) Telephone/chat counseling (e.g., Børnetelefonen or Headspace).

Response categories included “very likely,” “likely,” “unlikely,” “very unlikely,” and “don’t know/don’t have.”

The intention was to present the responders with a scenario that we consider to be of severity demanding support and help. Furthermore, a scenario related to symptoms of depression was chosen, as this is one of the most common issues among young people.

If participants indicate that they are unlikely or very unlikely to seek help from the listed sources of support, they are prompted to select their reasons from the following categories: (1) “I don’t think they can help me”; (2) “I prefer to handle it by myself”; (3) “I am afraid of burdening them”; (4) “I find it embarrassing/shameful to feel this way”; (5) “I have sought help but did not receive it”; (6) “I don’t believe I can get better”; or (7) “Other, please describe.” In addition, all participants are asked which factors might encourage them to seek help for mental health issues through an app or website and what barriers prevent them from doing so, explored through 4 different phrasings in open-text questions.

#### Other Measures of Mental Health and Well-Being

The Patient Health Questionnaire-4 (PHQ-4) is an ultrabrief self-report validated questionnaire that consists of a 2-item depression scale (Patient Health Questionnaire-2) and a 2-item anxiety scale (Generalized Anxiety Disorder-2). A validation study showed that the scale consists of 2 discrete factors (depression and anxiety) that explain 84% of the total variance [40]. An elevated PHQ-4 score is not a diagnostic tool but rather gives an indication of the presence of depression or anxiety.

The Short Form Perceived Stress Scale is an instrument for measuring perceived stress [41]. The Perceived Stress Scale-4 is designed to assess how unpredictable, uncontrollable, and overloaded respondents find their lives and provides a measure of an individual’s perceived stress levels.

The Body Appreciation Scale-2 (BAS-2) focuses on positive body image and not just body appearance. Since its release in 2015, the BAS-2 has been translated into more than 20 languages and is well-validated. BAS-2 consists of 10 items; however, the work by Tylka et al [42] demonstrated that 2 items explain more than 95% of the variance captured by the full 10-item questionnaire, named the BAS-2 Short Form. To shorten the survey, we decided to only include 2 items: “I feel love for my body” and “I am comfortable in my body.” We are using a Danish translation of the BAS-2, previously tested among people aged between 12 and 19 years [43]. BAS-2 has not yet been validated in a Danish context nor among people aged between 15 and 25 years; however, we are currently conducting this validation and will consider these results when interpreting our findings.

### Tests of Surveys and Setup

The initial survey was pilot-tested through cognitive interviews with 5 informants aged between 15 and 25 years. This process aimed to assess how the questions were interpreted and identify potential challenges in responding to the surveys [44]. Special attention was given to questions we had developed ourselves. On the basis of the informants’ feedback, the wording was adjusted for clarity, categories were refined to better capture expected answers, and some questions were omitted due to misinterpretations. In addition, as the preexisting scales for intentions of help seeking were found to be unfeasible, the researchers constructed a new scale for the study, inspired by preexisting scales and the informants’ comments. The constructed scale was tested among 4 new informants aged between 15 and 25 years and 2 from the initial test and adjusted accordingly.

Due to technical difficulties, an unplanned test phase of the survey setup was conducted. During this phase, 323 respondents, recruited via Facebook and Instagram, completed the T1 survey and were invited to participate in the follow-up surveys. The intervention group also received the SMS text message campaign invitation. However, technical errors led to some participants being invited for follow-up surveys at incorrect times, and most participants did not receive reminders for nonresponse. In addition, some participants in the intervention group received the SMS text message campaign invitation late or not at all. This phase allowed us to thoroughly assess the surveys. We reviewed all participants’ comments and corrected or omitted questions that did not work as intended.

### Sample Size Calculation

We performed a sample size calculation, considering an average effect size of 0.1 for mental well-being (on the WHO-5 scale) at T2 to be of public health relevance (it is equal to an improved WHO-5 score of 1.94 points on average in the intervention group compared to the control group). Even small effects on individual mental health outcomes can lead to a major impact at a population level, particularly when the service can be scaled widely and reach a large target audience.

We applied the conventional levels of statistical power (0.8) and level of significance (.05) and assumed an SD of 19.4 at T1 among the intervention and control groups combined (based on data from the feasibility study) [18]. On the basis of these assumptions, at least 3142 participants were required (n=1571, 50% in each group).

In the test phase, we retrieved a response proportion of 64.1% (323/504) at T2 (primary end point). Assuming a similar retention proportion, we aim to include 4910 participants. The proportion of participants responding to the follow-up surveys will be regularly reviewed to evaluate if the assumption regarding retention in the sample size calculation is correct or if the number of participants included should be increased or decreased.

### Planned Statistical Analysis

#### Overview

We will evaluate the effect of Mindhelper on multiple outcomes, as illustrated in Figure 3. First, we will conduct a randomization check and a dropout analysis. The primary analyses will follow the intention-to-treat principle, including all participants according to their randomized allocation, regardless of intervention use, and will be based on imputed data in cases of missingness. Missing data will be handled by multiple imputations using information from all the time points [45]. To test the robustness of the findings, sensitivity analyses will be conducted among complete cases. In addition, we will assess the complier average causal effect using the “contamination-adjusted intention-to-treat” method, an instrumental variable approach that accounts for adherence while preserving the benefits of randomization [46]. In this analysis, self-reported Mindhelper use at T4 in both the intervention and control groups will serve as the measure of adherence.

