**Use of the health care system**					
	Absence from work or school	✓	✓	✓	✓
	Contact with the health care system	✓	✓	✓	✓

^a^T1: baseline.

^b^T2: 2 weeks after randomization.

^c^T3: 6 weeks after randomization.

^d^T4: 12 weeks after randomization.

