#### The Effects of Mindhelper on Mental Well-Being and Psychological Functioning

The primary analysis will compare mean mental well-being, measured by WHO-5, between the intervention and control groups at T2, adjusted for WHO-5 scores at T1. If model assumptions are met, we will use a linear regression model. Psychological functioning, the secondary outcome measured by SWEMWBS, will be analyzed similarly as a continuous outcome, also adjusted for T1 values.

T2 was chosen for the primary assessment of effect because Mindhelper aims to provide immediate support and advice when problems arise. Most users visit thewebsite for a shorter period rather than regularly over multiple weeks. If the model assumptions are met, long-term effects will be evaluated at T3 and T4 using a repeated measures linear regression model.

To assess variation in effect by participants’ gender (male, female, or other) and socioeconomic background (parents’ highest educational attainment), analyses will be stratified accordingly. In addition, we will stratify by mental well-being at T1, expecting Mindhelper to be most effective for participants with moderate mental well-being (WHO-5 scores between 36 and 50) compared to those at high risk of depression or long-term stress (WHO-5 scores between 0 and 35) and those with mental well-being scores within the average range of the general population (WHO-5 scores >50). Furthermore, this stratified analysis will enable us to assess potential negative side effects of the intervention, assessing if the intervention group with WHO-5 scores >50 at T1 experienced a decline in mental well-being compared to the control group.

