### Conclusions

Individuals most commonly access Mindhelper via diagnostic and research-related search queries through search engines (eg, Google), where users are organically drawn to the content. In contrast, the Mindhelper study actively directs content to the intervention group. Therefore, our study deviates from the natural use patterns and evaluates the combined effects of the SMS text message campaign and Mindhelper. We create a situation that brings participants to Mindhelper, but Mindhelper and the use of Mindhelper are not designed for the intervention. Furthermore, conducting the study in Mindhelper’s natural use context would preclude the establishment of a control group, thereby making it impossible to evaluate its effects within the framework of an RCT.

A key challenge is expected to be adherence in the intervention group, meaning the extent to which participants in the intervention group engage with Mindhelper. Our feasibility study indicated (very) low engagement when participants were solely provided with a link to Mindhelper by the end of the T1 survey [18]. Therefore, the SMS text message campaign was developed, aiming to boost adherence; however, we do not know yet whether this was sufficient.

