Low adherence could lead to misclassification of exposure within the intervention group, potentially introducing bias into results. If nonadherence is unrelated to mental health outcomes (nondifferential misclassification), this misclassification could reduce observed intervention effects. However, if nonadherence is related to mental health outcomes (differential misclassification), this could either inflate or attenuate the observed effect, depending on adherence patterns. We will conduct sensitivity analyses based on the as-treated principle (complier average causal effect) to assess potential effects under full adherence. Adherence data will be collected in binary format (yes or no) at T2 to T4 for the intervention group. For the control group, adherence will be assessed at T1 and T4. In the feasibility study, participants’ self-reports on specific Mindhelper features used did not align with their actual web history [18]. Therefore, we have revised our approach, asking the intervention group to describe how they have used Mindhelper and Ro apps in open-text questions, which will be coded with natural language processing models. Furthermore, qualitative information will provide insights into participant engagement and reasons for nonuse, and aggregated data on participants’ interaction with the SMS text message campaign will provide information on adherence.

It must be noted that the self-guided nature of Mindhelper and the diversity of topics covered mean that adherent participants in the intervention group may engage with different content and receive varying “doses” of the intervention, which aligns with the real-world application but makes the evaluation more complex.

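### The complier analysis takes Mindhelper use at week 12 as adherence without limiting this to week-12 outcomes, although the primary and secondary outcomes are at week 2, and the Discussion mislabels it as as-treated

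*Protocol article*

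**What the plan says.** Under Planned Statistical Analysis, Overview, the protocol article adds a CACE to the intention-to-treat analysis, using contamination-adjusted intention-to-treat. It describes this as "an instrumental variable approach that accounts for adherence while preserving the benefits of randomization" and specifies that "self-reported Mindhelper use at T4 in both the intervention and control groups will serve as the measure of adherence". It does not say which outcome wave the CACE addresses.

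The primary analysis compares mean WHO-5 "between the intervention and control groups at T2, adjusted for WHO-5 scores at T1". SWEMWBS is analysed in the same way, and body appreciation is also first compared at T2. The footnotes to Table 1 give "T2: 2 weeks after randomization" and place T4 at 12 weeks. The reason for the early endpoint is stated: "T2 was chosen for the primary assessment of effect because Mindhelper aims to provide immediate support and advice when problems arise".

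On data collection, the Discussion (under Conclusions) says "Adherence data will be collected in binary format (yes or no) at T2 to T4 for the intervention group". For controls it gives T1 and T4 only, and Table 1 agrees.

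The same part of the Discussion describes the analysis differently: "We will conduct sensitivity analyses based on the as-treated principle (complier average causal effect) to assess potential effects under full adherence". It also says that the trial "evaluates the combined effects of the SMS text message campaign and Mindhelper".

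**The concern.** An instrumental-variable complier estimate divides the effect of assignment by the between-arm difference in exposure. For a week-2 outcome, the relevant exposure is what happened by week 2. The text messages run through the study and keep prompting use, so some participants may first use Mindhelper between weeks 2 and 12. If the T4 item covers all use so far, they count as compliers although they were unexposed when the outcome was measured. If it covers only recent use, early users who stopped count as non-users. The article says that most users visit for a short period, so that group could be sizeable.

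The article names adherence as a key challenge, and the CACE is its planned estimate of what Mindhelper does when it is used. A complier effect with mismatched timing would be easy to misread.

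The label is a second, separate problem. An as-treated analysis regroups participants by actual use and gives up the protection of randomisation, which the Overview says is kept. A CACE is an effect among compliers. It is not the effect if everyone adhered.

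**Working it through.** **The protocol's own figures.** There is none for the complier analysis. The planning difference reproduces: 0.1 × 19.4 = 1.94 WHO-5 points. So does the sample size: at two-sided .05 and power 0.8 a t-test needs 1570.7 per arm, hence 1571 per arm and 3142 in total. Neither depends on this point.

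**Timing, side by side.**

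| Item | Intervention arm | Control arm |
|---|---|---|
| WHO-5, SWEMWBS: main comparison | T2 (week 2) | T2 (week 2) |
| Mindhelper use collected | T2, T3, T4 | T1, T4 |
| Use entered in the CACE | T4 (week 12) | T4 (week 12) |

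T4 is the only follow-up with use from both arms.

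**Formula.** CACE = ITT effect ÷ (proportion using in the intervention arm − proportion using in the control arm). For a T2 outcome the numerator is fixed at T2. Replacing the T2 difference in use by the T4 difference leaves the result unchanged only if the two differences are equal.

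**Direction, with assumed uptake.** The article gives no uptake rates, so every percentage below is an assumption and shows direction only. The ITT effect is set to the planning value of 1.94.

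| Use by T2 (int. / control) | CACE with T2 use | Use reported at T4 (int. / control) | CACE with T4 use |
|---|---|---|---|
| 30% / 2% | 1.94/0.28 = 6.93 | 30% / 2% (no change) | 6.93 |
| 30% / 2% | 6.93 | 40% / 3% (cumulative) | 1.94/0.37 = 5.24 |
| 30% / 2% | 6.93 | 50% / 5% (cumulative) | 1.94/0.45 = 4.31 |
| 50% / 2% | 1.94/0.48 = 4.04 | 60% / 5% (cumulative) | 1.94/0.55 = 3.53 |
| 30% / 2% | 6.93 | 15% / 2% (recent use, declining) | 1.94/0.13 = 14.92 |

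A cumulative item pulls the estimate down when the difference in use has grown. A recent-use item with falling use pushes it up. The article does not give the item's recall window, so the direction cannot be settled from it.

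**Can the missing T2 control value be handled?** Take the third row. Control use by T2 is unmeasured but lies between 0 and the 5% reported at T4. The bracket is 1.94/0.30 = 6.47 to 1.94/(0.30 − 0.05) = 7.76. It contains 6.93, the value with true T2 use, and excludes 4.31, the value with T4 use. The upper limit is valid only if the control item at T4 covers all use since randomisation.

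**The case against.** Several objections stand.

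- **The analysis is supportive.** It is added after the intention-to-treat analysis, and the Discussion calls it a sensitivity analysis. A ratio estimator rescales the intention-to-treat effect, so changing the denominator leaves the test of no effect essentially as it was.
- **T4 follows from the data.** The method needs use in both arms, and only T4 has it at follow-up. The article does not give this reason, but it is the likely one.
- **The mismatch is partly inferred.** The CACE outcome wave is not named, and for T4 outcomes the problem disappears. The article cites a detailed analysis plan, not shown here, which may specify the wave and the item. As written, however, the article fixes T4 use without restriction, beside analyses whose main time point is T2.
- **A diluted estimate is not an invalid one.** With a cumulative item, the ratio is the average week-2 effect among those induced to use Mindhelper by week 12. That is interpretable, but it is not the effect in those exposed before the outcome.
- **Use may be front-loaded.** The intervention arm is directed to the website at the end of the baseline survey, which could narrow the gap between T2 and T4. Against that, the feasibility study found very low engagement with a link alone.

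A reader might go further than the document allows:

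- *That the complier effect is wrong by a known amount.* No uptake rates are given, so no percentage error can be stated.
- *That a confounded as-treated comparison will be run.* The same sentence specifies a CACE and the Overview names the instrumental-variable method, so this is more likely a wording error.
- *That the text messages invalidate the instrument.* They carry tips on using Mindhelper and link into its website, so they are mainly a route to the service. An effect without use is possible and belongs among the limitations. Relabelling the estimate would not remove it.
- *That reliance on T4 responders undermines the analysis.* Multiple imputation using all time points is planned and partly answers this.

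**Conclusion.** The point holds as a moderate correction to a supportive analysis. For the T2 outcomes, adherence measured at T4 does not match exposure before the outcome unless the between-arm difference in use is the same at weeks 2 and 12. The estimate is diluted if the T4 item is cumulative and that difference grows, and may be inflated if the item captures only recent use that has declined. The size cannot be given.

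This assumes that the CACE is meant to cover T2 outcomes, which is the natural reading because it sits beside the primary analysis. Outcomes at T3, including the main help-seeking comparison, have the same mismatch over a shorter gap.

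The as-treated and full-adherence wording contradicts the Overview and needs correcting whatever is decided on timing. The primary intention-to-treat result and the sample size are unaffected.

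**What to change.** 1. State the outcome wave for each CACE and match use to it.
   - **T2 outcomes:** define intervention-arm adherence as use reported at T2. Bracket control use by T2 between 0 and the control proportion reporting use at T4, and report the CACE at both ends.
   - **T3 outcomes:** take intervention-arm use up to T3, with the same control bracket.
   - **T4 outcomes:** take cumulative use up to T4 in both arms.
2. State the recall window of the T4 item. If it covers only recent use, say that the control proportion is not a firm upper limit.
3. In the Discussion, remove the as-treated and full-adherence wording and describe the estimate as the effect among compliers. Note as a limitation that the text-message campaign may act without any use of Mindhelper.

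The cost is small if this is done before unblinding, because intervention-arm use at T2 and T3 and control use at T4 are already in the surveys. Control use by T2 and T3 is not measured, so the T2 and T3 results become a range instead of a single CACE value.

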**Figure 3 figure3:**
[figure not shown]
Overview of the planned analysis.

Analyses of data and interpretation of results will be done masked to the participant allocation. No interim analysis will be conducted during the trial. The subsequent section outlines the planned statistical analysis of each outcome and the cost-effectiveness analysis. A detailed statistical analysis plan has been published [47] before initiating any outcome analyses and unblinding the data.

#### The Effects of Mindhelper on Mental Well-Being and Psychological Functioning

The primary analysis will compare mean mental well-being, measured by WHO-5, between the intervention and control groups at T2, adjusted for WHO-5 scores at T1. If model assumptions are met, we will use a linear regression model. Psychological functioning, the secondary outcome measured by SWEMWBS, will be analyzed similarly as a continuous outcome, also adjusted for T1 values.

T2 was chosen for the primary assessment of effect because Mindhelper aims to provide immediate support and advice when problems arise. Most users visit thewebsite for a shorter period rather than regularly over multiple weeks. If the model assumptions are met, long-term effects will be evaluated at T3 and T4 using a repeated measures linear regression model.

To assess variation in effect by participants’ gender (male, female, or other) and socioeconomic background (parents’ highest educational attainment), analyses will be stratified accordingly. In addition, we will stratify by mental well-being at T1, expecting Mindhelper to be most effective for participants with moderate mental well-being (WHO-5 scores between 36 and 50) compared to those at high risk of depression or long-term stress (WHO-5 scores between 0 and 35) and those with mental well-being scores within the average range of the general population (WHO-5 scores >50). Furthermore, this stratified analysis will enable us to assess potential negative side effects of the intervention, assessing if the intervention group with WHO-5 scores >50 at T1 experienced a decline in mental well-being compared to the control group.

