**Secondary outcome**					
	The Short Warwick-Edinburgh Mental Well-Being Scale	✓	✓	✓	✓

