**Other measures of mental health and well-being**					
	Patient Health Questionnaire-4	✓	✓	✓	✓
	The Short Form Perceived Stress Scale-4	✓		✓	✓
	Body Appreciation Scale-2 Short Form	✓	✓	✓	✓
	Diagnosed with a mental health issue	✓		✓	✓
	Affected by a diagnosis within the last month	✓		✓	✓
	Treated for diagnosis within the last month	✓		✓	✓

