#### Cost-Effectiveness Analysis

The cost-effectiveness analysis will be performed by constructing a standard incremental cost-effectiveness ratio (ICER) expressing the additional cost per mean mental well-being score, measured by WHO-5, obtained from the randomization to Mindhelper compared with standard care [49]. The analysis will apply standard techniques from economic evaluation aimed at estimating costs per quality-adjusted life years gained. The results from this analysis will contribute to the evidence-based economic evaluation of interventions aimed at increasing mental health and well-being.

Incremental estimates of costs and mental well-being scores obtained will be assessed in a regression model. To examine the second-order uncertainty of the estimated ICERs, a probabilistic sensitivity analysis using a 5000 bootstrap resample with a 95% CI will be conducted. Cost-effectiveness planes illustrating the resampled ICERs and cost-effectiveness acceptability curves at T2 to T4 will be constructed to show the probability that the intervention is cost-effective given varying threshold values for an additional change in the mean mental well-being score obtained. No standardized fixed threshold for the value of an additional mean mental well-being score obtained from a new health intervention exists. Therefore, the probability of cost-effectiveness will be investigated for several thresholds, for example, values ranging from 0 to DKK 500,000 (US $78,038.43).

Both potential health care savings and direct costs of delivering the intervention will be included in the analysis. Information on self-reported all-cause demand for acute health care services, general practitioner visits, use, and absence from employment in the project period will be gathered from surveys. To operationalize this in monetary terms, the average unit cost of acute health care use and average hourly wage earnings depending on gender and age in Denmark will be used in the economic evaluation. For the intervention group, operating costs related to Mindhelper will also be included based on the overall cost per user. These costs cover development, maintenance, and technical support for the service. Cost estimates will be calculated based on list prices from health care providers, and scenarios of changes in the number of users will be explored.

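### The primary model is valid but names only T1 WHO-5 as a covariate; prespecifying other T1 measures already collected would give a small, free gain in precision

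*Protocol article*

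**What the plan says.** The section on mental well-being and psychological functioning defines the primary analysis as a comparison of mean WHO-5 "between the intervention and control groups at T2, adjusted for WHO-5 scores at T1". On model type it says: "If model assumptions are met, we will use a linear regression model". It names no other covariate. Gender, parental education and T1 WHO-5 band appear there as strata for subgroup analyses, not as covariates.

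Table 1 shows what else is taken at T1: "The Short Warwick-Edinburgh Mental Well-Being Scale", the PHQ-4, "The Short Form Perceived Stress Scale-4", diagnosis of a mental health issue, gender and age. The Study Design section says that only people who complete the T1 survey can be invited to follow-up, so these values should be close to complete among those followed.

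The Overview of the Planned Statistical Analysis bases the primary analysis on multiple imputation that draws on all time points. It adds that "sensitivity analyses will be conducted among complete cases". It also refers to a detailed SAP, published before any outcome analysis or unblinding.

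**The concern.** T1 WHO-5 is a single five-item score and so carries measurement error. SWEMWBS measures a closely related construct, and PHQ-4 and PSS-4 measure distress and stress. Together with diagnosis, gender and age they may predict T2 WHO-5 beyond what T1 WHO-5 does. In a linear model with about 3000 responders, adding prespecified prognostic covariates does not bias the treatment effect and usually narrows its interval.

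Two things are at stake, both modest. The first is precision on a target effect of 0.1 SD. The second is the complete-case check. About 36% are expected to be missing at T2, and the article itself warns that nonrandom dropout could push the result either way. If the added variables drive dropout differently by arm, a complete-case model without them is a weaker check on the imputed result.

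**Working it through.** **1. The plan's own figure.** Inputs from the Sample Size Calculation section: "it is equal to an improved WHO-5 score of 1.94 points on average in the intervention group compared to the control group"; "assumed an SD of 19.4 at T1 among the intervention and control groups combined"; power 0.80; alpha 0.05, taken as two-sided.
- Normal formula: n per arm = 2 × (1.960 + 0.842)² / (1.94/19.4)² = 2 × 7.849 / 0.01 ≈ 1570. The t-test version gives 1570.7, rounded up to 1571, or 3142 in total. This matches.
- Enrolment: 3142 / 0.64 ≈ 4910. This matches.

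No credit for baseline adjustment enters this calculation.

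**2. Precision under the plan's model.** The T1-T2 WHO-5 correlation r is not in the document. With r = 0.60 assumed and 1571 per arm:
- Unadjusted SE = 19.4 × √(2/1571) = 0.692; power for 1.94 points is 80.0%.
- Adjusted for T1 WHO-5: SE = 0.692 × √(1 − 0.36) = 0.554; 1.94/0.554 = 3.50; power is about 94%.
- Over r = 0.4, 0.5, 0.6 and 0.7, power under the plan's model is 86.4%, 89.9%, 93.9% and 97.5%.

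**3. Adding the three scales (SWEMWBS, PHQ-4, PSS-4).** Correlations are assumed and taken in the direction of better well-being. The four T1 scales correlate c = 0.70 with each other. T2 WHO-5 correlates 0.60 with T1 WHO-5 and 0.50 with each added scale.
- R² = r′R⁻¹r, which for equal inter-scale correlation is [Σr² − c/(1 + 3c) × (Σr)²] / (1 − c).
- Σr² = 0.36 + 3 × 0.25 = 1.11; (Σr)² = 2.1² = 4.41; c/(1 + 3c) = 0.7/3.1 = 0.2258.
- R² = (1.11 − 0.9958)/0.30 = 0.381, against 0.360 for T1 WHO-5 alone.
- Fall in residual variance: 1 − 0.6194/0.64 = 3.2%.
- SE = 0.554 × √0.968 = 0.545, so the interval is 1.6% narrower. Power is about 94.5%.
- Equivalent completers: 3142 × (1/0.968 − 1) ≈ 105. At 64% retention this is about 165 enrolled.

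**4. Range.** I varied r over 0.55-0.70, c over 0.60-0.75, and the added scales' correlation with T2 WHO-5 over 0.45-0.55. The fall in residual variance runs from 0 to about 15%, with one extreme corner (0.55, 0.60, 0.55) at 19%. A second route, adding 0.02-0.05 to R² at r = 0.6, gives 3.1-7.8%. Diagnosis, gender and age are not counted and could add something.

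**5. Complete-case check.** This is an illustrative simulation with 64% retention, a true effect of 1.94 and one extra T1 variable that predicts both outcome and dropout.

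| Dependence of dropout on the extra variable | T1 WHO-5 only | Extra variable added |
|---|---|---|
| Same in both arms | 1.98 | 1.97 |
| Differs by arm (log-odds shift ±0.1 to ±0.3 per SD) | 2.08 to 2.31 | 1.91 to 1.95 |

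In the worst row the drift is 2.31 − 1.94 = 0.37 points, about a fifth of the target effect. With equal dependence there is nearly nothing to protect against.

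**The case against.** The strongest reply is that nothing here is wrong. Adjusting for the outcome's own baseline value is standard and unbiased under randomisation, and it already captures most of the available gain. That stands in full.

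Second, the article excludes no further covariates. It points to a published SAP that may list them and may already use these variables in the imputation model. That also stands, so the recommendation is conditional on what the SAP says.

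Third, the size rests wholly on assumed correlations, and the range starts at zero. This is true, and it keeps the point small.

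Fourth, changing a published primary model has an administrative price. It does, but the change needs no new data and the present model is kept beside it.

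Three stronger readings are tempting and are not supported.
- A reader might infer that the trial is short of power because it seeks 0.1 SD at 80%. The 80% uses the raw SD, and the plan's own model already gives about 94% at r = 0.6.
- A reader might infer that the complete-case analysis is invalid unless dropout depends on nothing but arm and T1 WHO-5. That is too strict: harm arises mainly when dependence on an omitted prognostic variable differs by arm. The analysis is also a sensitivity check, not the primary analysis.
- A reader might infer that the cost-effectiveness regression is unadjusted. The article says "Incremental estimates of costs and mental well-being scores obtained will be assessed in a regression model" and neither names nor excludes covariates. The complier and mediation analyses are likewise described without stated T1 adjustment, so this silence is condensation and shows no defect.

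**Conclusion.** The point holds as an optional but worthwhile efficiency improvement. The article names one baseline covariate for the primary model while several other likely prognostic measures are collected at the same survey from everyone who enters follow-up. Under assumed correlations the added covariates cut residual variance by about 0-15%. In the middle case the SE moves from 0.554 to 0.545 and power rises by about half a percentage point.

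The added protection of the complete-case check is conditional on arm-differential dropout. That is plausible here, since only the intervention arm receives the SMS campaign and controls are told their allocation, but the document gives no evidence that it occurs. The validity of the primary analysis and its planned power are not in question.

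**What to change.** Before unmasking, fix these covariates for the primary model: T1 WHO-5, SWEMWBS, PHQ-4, PSS-4, diagnosis (yes/no), gender and age. Use the same variables as predictors in the imputation model and as covariates in the complete-case check. Report the model with T1 WHO-5 alone as a sensitivity analysis. If the published SAP already specifies this, only the article's wording needs aligning; if not, record a dated SAP amendment made before unmasking.

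The cost is a sentence or two in each document and about 7 degrees of freedom (one each for the three scales, diagnosis and age, two for gender) out of more than 3000. No new data are needed.
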